## Abstract

**Background:**

Treatment of a child who has an anxiety disorder usually begins with the question of which treatment to start first, medication or psychotherapy. Both have strong empirical support, but few studies have compared their effectiveness head-to-head, and none has investigated what to do if the treatment tried first isn’t working well—whether to optimize the treatment already begun or to add the other treatment.

**Methods:**

This is a single-blind Sequential Multiple Assignment Randomized Trial (SMART) of 24 weeks duration with two levels of randomization, one in each of two 12-week stages. In Stage 1, children will be randomized to fluoxetine or Coping Cat Cognitive Behavioral Therapy (CBT). In Stage 2, remitters will continue maintenance-level therapy with the single-modality treatment received in Stage 1. Non-remitters during the first 12 weeks of treatment will be randomized to either [1] optimization of their Stage 1 treatment, or [2] optimization of Stage 1 treatment and addition of the other intervention. After the 24-week trial, we will follow participants during open, naturalistic treatment to assess the durability of study treatment effects. Patients, 8–17 years of age who are diagnosed with an anxiety disorder, will be recruited and treated within 9 large clinical sites throughout greater Los Angeles. They will be predominantly underserved, ethnic minorities. The primary outcome measure will be the self-report score on the 41-item youth SCARED (Screen for Child Anxiety Related Disorders). An intent-to-treat analysis will compare youth randomized to fluoxetine first versus those randomized to CBT first (“Main Effect 1”). Then, among Stage 1 non-remitters, we will compare non-remitters randomized to optimization of their Stage 1 monotherapy versus non-remitters randomized to combination treatment (“Main Effect 2”). The interaction of these main effects will assess whether one of the 4 treatment sequences (CBT➔CBT; CBT➔med; med➔med; med➔CBT) in non-remitters is significantly better or worse than predicted from main effects alone.

**Discussion:**

Findings from this SMART study will identify treatment sequences that optimize outcomes in ethnically diverse pediatric patients from underserved low- and middle-income households who have anxiety disorders.

**Trial registration:**

This protocol, version 1.0, was registered in ClinicalTrials.gov on February 17, 2021 with Identifier: NCT04760275.

## Background

Anxiety disorders are highly prevalent in children, adolescents, and young adults. Approximately 12.3% of children meet formal diagnostic criteria for an anxiety disorder by age 12, and an additional 11% meet criteria by age 18, most commonly social anxiety, separation anxiety, and generalized anxiety disorders [1]. Most adult anxiety disorders begin in childhood or adolescence [2–4], suggesting that early intervention may reduce anxiety prevalence in adults, attenuate the frequent worsening of symptoms and lessen the associated impairment over time [1, 5, 6]. Early treatment of pediatric anxiety disorders may also mitigate the development or functional impact of common comorbid disorders [7, 8], including depression [1], Attention-Deficit/Hyperactivity Disorder (ADHD) [9], oppositional defiant or conduct disorder [10], substance abuse [5, 11, 12], and suicide attempts [13, 14]. More broadly, anxiety disorders confer considerable risk for lifetime impairments in overall quality of life, interpersonal relationships, physical health, finances, and academic and occupational functioning [1, 6]. They are strongly associated with years of life lost and lived in disability, especially when beginning in childhood [15].

Systematic reviews and meta-analyses have consistently shown that pediatric anxiety disorders, like their adult counterparts, are chronic, recurrent, and unstable in their diagnostic classification over time, with new anxiety disorders appearing together with or replacing the initial, primary diagnosis [16, 17], suggesting strongly that clinical trials should consider multiple anxiety disorders and aggregate symptom outcome measures. Systematic reviews and meta-analyses have also documented substantial therapeutic effects for both psychotherapy, particularly CBT (Cognitive Behavioral Therapy) [18, 19], and medication, especially SSRIs (selective serotonin reuptake inhibitors) [20–22]. While response rates to acute treatment near 60% for both CBT [23] and SSRIs [21, 22] may seem encouraging, these rates also mean that approximately 40% fail to respond. Remission rates are lower, 40–50% for both CBT [24] and SSRIs [21, 22], and even poorer in real-world, community settings (20–40%) [25–27]. Long-term follow-up in pediatric studies is rare, but data suggest that outcomes are poor and relapses common, similar to what is observed in adult anxiety disorders, where relapse approaches 60% [16, 28]. Even after gold-standard treatments in the CAMS study (Child/Adolescent Anxiety Multimodal Study) – the largest and most rigorous combined medication and CBT trial thus far – 30% were chronic non-responders and an additional 50% relapsed at least once in 4 years, despite receiving post-trial treatment [29]. Racial/ethnic minorities in the CAMS study had significantly lower remission rates in all treatment arms [30]. Long-term outcomes did not vary according to initial treatment with CBT, medication, or their combination. Predictors of poor acute treatment outcomes include more severe symptoms, more functional impairment [29, 31], low socioeconomic status (SES) [32], and a primary diagnosis of social phobia [31, 32]. More residual symptoms and functional impairment following acute treatment predict relapse, suggesting that treatment should aim to achieve remission from all anxiety disorders, and with as few residual symptoms of any kind of anxiety as possible [29]. These predictors of relapse have informed our requirements for, and definition of, clinical remission during this trial.

### Gaps in evidence this study will fill

Although many studies have separately evaluated the efficacy and effectiveness of medication and CBT in the treatment of pediatric anxiety disorders, very few have compared the effectiveness of CBT and medication head-to-head [33] (the CAMS study did, but it was an efficacy study conducted in academic centers rather than in “real world” community clinics [10]). No studies have assessed whether it is preferable to begin with CBT and then add medication if needed, or begin with medication and then add CBT if needed. Our preliminary survey of clinicians, patients, and parents indicates that treatment of essentially every child with anxiety disorder begins with the vexing question of which modality to begin first. Considerations include: challenges in finding skilled CBT therapists; inconvenience of getting the child to weekly therapy; often-greater expense of CBT from more frequent co-pays; and resistance of the child (and sometimes a parent) to the structure, effort, and discomfort that CBT requires (e.g., in response to planned anxiety exposures). Modality decisions are also influenced by the wish to avoid medication in a child [34], with its under-studied, long-term side effects [35], and concern about relapse after discontinuation [20, 36, 37]; the perception that medication may be less emotionally supportive than psychotherapy; the stigma often associated with medication [38]; or the perception that medication is a “crutch” that instills physical and psychological dependency [39], unlike the skills that CBT aims to impart. Ethnic minorities often have a cultural aversion to medication, particularly for mental health problems, and especially in children [39, 40], but they also tend to view CBT as less feasible for their lifestyle [40], thereby limiting their treatment adherence [41]. Complicating the selection of initial treatment is the absence of data indicating whether sequencing of treatment impacts treatment satisfaction, well-being, peer relationships, parent and family functioning, school functioning, or comorbid psychiatric symptoms [5, 42–44]. Finally, few studies have adequately tested the effectiveness of either treatment modality in the complex and underserved families who are likely disproportionately affected by anxiety disorders. Empirical data for the effectiveness of anxiety treatments in underserved families are particularly sparse for patient-centered outcomes and for the head-to-head comparison of CBT to medication. In the CAMS trial comparing CBT to medication, for example, the patient sample was 78% Caucasian and 75% middle or upper class [10]. A recent AHRQ (Agency for Healthcare Research and Quality) review identified inadequate ethnic and racial diversity as a prominent limitation of prior treatment studies of pediatric anxiety disorders and stressed that characterizing treatment response in underserved ethnic minorities, and identifying modifiers of treatment response, constitute the most pressing needs for future research [20].

Consensus panels formulating treatment guidelines for pediatric anxiety disorders have relied on clinical experience, theory, and findings from observational and controlled trials of CBT or medication conducted in isolation for other purposes. They generally agree that CBT and either SSRI or SNRI pharmacotherapies have the strongest evidence for efficacy [20]. They often recommend CBT as the first-line treatment, but without evidence that it yields better patient outcomes than beginning with medication [44–46]. Many guidelines recommend combining psychological and medication therapy after an unsatisfactory initial treatment response, but without evidence that combined therapy is better than continuing or intensifying the initial treatment. Very few studies have compared combined therapy to either treatment alone [47–49]. In the CAMS study, combined CBT + sertraline improved clinical response more than either modality alone [49], but primarily in those with severe anxiety [50], and not in long-term follow-up [29].

To address these gaps in evidence for development of treatment guidelines for pediatric anxiety disorders, we will conduct a Sequential Multiple Assignment Randomized Trial (SMART) [51, 52], that will develop and test an *Adaptive Intervention –* a set of decision rules for adapting treatment according to a patient’s individual clinical response – for the initial selection of treatment modalities (CBT or SSRI) and their subsequent sequencing, combination, and maintenance in treating pediatric anxiety. These rules will be based on individual patient characteristics -- particularly the patient’s response to initial and subsequent treatment, but also demographic and clinical characteristics -- that optimize treatment response. The SMART design involves randomization of participants at least once, and often more than once, sequentially over the course of the trial. Randomization occurs at critical decision points depending on the patient’s clinical response and is used to provide valid causal inference about the effects of differing interventions that will inform treatment decisions [53, 54]. This design provides a rigorous framework in which to develop evidence-based treatment algorithms. SMART designs make no a priori assumptions about the existence or form of delayed treatment effects [51, 52], making them ideal for developing an adaptive intervention that optimizes outcomes based on patient treatment history [51–54]. The SMART design described here – the first of its kind of which we are aware -- will focus on identifying treatment sequences that optimize patient centered outcomes for pediatric anxiety disorders in ethnically diverse patients from underserved low- and middle-income households.

### Conceptual framework of the SMART design

The conceptual framework for this study is founded on the observation that patients differ in their responses to treatment, presumably due to individual variability in the psychological, biological, cultural, and psycho-physiological factors that shape adaptive and maladaptive anxiety responses to life experiences [55]. Ample evidence documents dysfunction across the neural, cognitive, affective, and behavioral components of anxiety disorders. Less is known about the most effective ways to modify that dysfunction through treatment. Evidence suggests that CBT or medication can modify the cascade of responses to real or perceived threat – CBT by altering behavioral avoidance and information processing related to threat detection and coping [56, 57], and medication by altering neurotransmitter levels that affect the function and structure of brain circuits [58–60]. By experimentally controlling the sequencing of treatment modalities, we aim to advance knowledge about the relative merits of targeting the cognitive and behavioral components of this cascade with CBT, or its biological components more directly with medication.

Individual differences in treatment response likely derive from patient-specific biological, sociological, psychological, historical, and contextual determinants of responses to threat [61]. For a treatment to be most effective, it should be tailored to patient characteristics that influence those determinants. Tailoring should be adapted dynamically, repeatedly over time according to that patient’s individual response to treatment, to produce an adaptive intervention that informs how and when to intervene, and how and when to modify the intervention to optimize long-term outcomes. An adaptive intervention has 4 components: (1) decision stages, each beginning with a decision concerning treatment; each decision stage incorporates (2) treatment options, (3) tailoring variables, and (4) an if/then decision rule. The decision stages, treatment options, tailoring variables, and implementation of decision rules *are all part of the intervention itself* [62]. The overarching aim and function of a SMART design is to construct a high-quality adaptive intervention based on empirical data. A SMART design builds an adaptive intervention that dynamically tailors treatment to individual patient characteristics and evolving therapeutic response to optimize patient outcomes, a process that has been likened conceptually and operationally to the development of a feedback control system for dynamic systems that regulates and optimizes a time-varying study outcome variable [63]. A SMART design offers a considerable practical advantage over more traditional trial designs, in that it addresses simultaneously several research questions and study hypotheses relevant to each decision stage, as well as their interaction representing the sequencing of interventions [64].

#### Patient-centeredness within the SMART design

Adaptive interventions resemble clinical practice, in that different interventions are assigned to different individuals and within individuals over time, with the intervention(s) ideally varying in response to patient needs and patient response [62]. Clinicians, however, often lack the empirical evidence needed to guide such intervention. In pediatric anxiety treatment, limited evidence exists to inform the decision about which treatment to begin with based on a particular patient’s characteristics and context, and what the clinician should do if the chosen treatment is not working. This absence of empirical data for clinical decision-making is a challenge that may be addressed in part via the multistage randomization of a SMART design to inform the development of optimal adaptive interventions, providing an empirical basis for clinical decision-making. The relevance to pediatric anxiety is clear: though substantial evidence supports the effectiveness of both SSRI’s and CBT in treating pediatric anxiety, neither treatment works well for all youth, and much more evidence is needed to guide clinician judgments regarding *which* treatment to use, with *which* patients, and at which points in treatment. The present study will address this gap, providing evidence to inform treatment-personalizing decisions that are required of virtually every clinician treating pediatric anxiety. Findings on the association of baseline individual tailoring and environmental variables with later clinical outcomes can inform the use of individual patient information for initial treatment assignment. Findings of the sequential randomization aspect of the SMART design during treatment can inform clinician decisions about treatment sequencing based on the individual patient’s response to the intervention currently in use, further supporting personalized treatment [53, 54]. Empirical evidence contributing to individualized treatment regimens based on tailoring variables, treatment history, and current response status will have the added advantage of supporting shared decision-making by the child and parents with an empirically-informed clinician [65, 66], ideally improving patient satisfaction, treatment motivation [67], and clinical outcomes [68, 69]. This study will also explore the effects of treatment on long-term patient and family-centered outcomes, such as symptom recurrence, subjective distress and well-being, social relationships, family and school functioning, and potential adverse treatment effects [20, 70]. The findings of this study will therefore inform decisions among patients, families, clinicians, and healthcare leaders about improvements that can be expected in the short- and long-term when treating pediatric anxiety disorders with CBT, medication, or their combination in real-world settings, providing information needed when making critically important treatment choices for individual patients, with a much-needed emphasis on children from underserved and minority populations.

#### Potential for study findings to be adopted into clinical practice and to improve delivery of care

Because adaptive approaches approximate intervention sequences used in clinical practice, they can be used to develop, test, and refine algorithms for clinical decision-making and inform the development and validation of practice guidelines [64]. The adaptive intervention that a SMART design produces can be incorporated into clinical practice more naturally and seamlessly than the findings of a fixed-intervention study [53, 54, 62].

### Hypothesized causal pathways and their theoretical basis in the treatment of pediatric anxiety disorders

Our study population will be predominantly economically disadvantaged, racial and ethnic minority youth, 8–17 years of age. The causal pathways from treatment assignment to clinical outcomes involve factors that are both common and specific to our two interventions (*Coping Cat* CBT and SSRI therapy) **(**Fig. 1**)**. *Coping Cat* CBT, like most psychological or behavioral therapies (henceforth “psychotherapies”), is a complex intervention comprising many elements. Some of those elements are present, to varying degrees, in most or all psychotherapies or even any clinical encounter, including an encounter when prescribing medicine [71, 72]. Some elements are considered unique and specific to CBT [73–75]. We propose to study both the common elements of the clinical encounter as well as elements specific to CBT in this SMART study. Of the many potential factors common to all clinical encounters, two are explicitly components of *Coping Cat* CBT, “alliance-building” and “reward”, and they are at least implicitly components of the psychopharmacological treatments as well **(**Table 1**)**. Two factors are generally considered unique to CBT, “exposure” and “coping efficacy”, or skill building [77, 78]. All four are thought to be important in improving patient outcomes: they are considered to be the “active ingredients” of the complex intervention, and to evolve over the course of the therapy. The extent to which these elements or functions are present in the therapy and increase over time is the extent to which patients are thought to improve. Therefore, we will measure these elements over time in this SMART study and assess their influence on patient outcomes.

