Exposure also promotes the development of cognitive, emotion regulation, and behavioral skills for coping more effectively with fear, termed *coping efficacy.* Coping efficacy diminishes the conditioned fear response and provides the opportunity for new extinction learning, with an attendant inhibition of maladaptive avoidance. Practicing these skills in different fear-inducing contexts supports generalization of inhibitory learning and stronger extinction of fear responses [78]. Of note, both time spent in exposure tasks, and level of difficulty of the exposures tolerated, predicted better outcomes to *Coping Cat* within the CAMS sample [119]. These findings directly informed our decision to have additional exposure practice and mastery be the focus of our Phase 2 CBT optimization protocol. In addition, efficacy measures in the CAMS trial outperformed specific measures of cognitive change in mediational models on Coping Cat effects, suggesting that development of coping efficacy may mediate CBT outcomes [120].

We will obtain after each CBT session a therapist-rated measure of 3 key facets of exposure practice (quantity, difficulty level, and mastery of exposure tasks) [119], which we will use to craft an index of tolerance to exposure – a CBT-specific factor in effecting patient outcomes. As a complement to this in-session measure of tolerance of exposure, we will also obtain at baseline and then every fourth session the parent version of the 8-item *Child Anxiety Avoidance Scales* [110], a measure of the evolving real-world CBT skill set outside of session that assesses the reduction of anxious avoidance when presented with threatening stimuli. Finally, we will use our measure of Self-efficacy from the NIH toolbox measure of Life-Satistfaction as a proxy for coping efficacy to test this CBT-specfic pathway. We expect that measures of each of the common factors will independently and positively associate with outcomes in our study for both *Coping Cat* and medication therapies [72, 82, 121], and we expect that the greater therapeutic alliance anticipated with CBT compared with medication therapy will partially mediate differences in clinical outcomes across the two treatment modalities. We also expect that measures of the CBT *specific factors* -- exposure tolerance and coping efficacy -- will positively associate with clinical outcomes in response to *Coping Cat* CBT.

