### Sample size and power

SMART designs are commonly but incorrectly assumed to require prohibitively large sample sizes [54]. It is common to think, for example, that data from a study design such as ours will be analyzed in a 6-way ANCOVA that compares outcomes across all 6 subgroups, which would indeed likely require a large sample size. That analysis, however, does not correspond with our primary aims and hypotheses, which are tested as two main effects and their interaction, and which require a sample size considerably smaller than for a 6-way ANCOVA [54]. We have made it our priority to identify a sample size that will allow us to test Stage 2 effects with sufficient power. We obtained the estimates of effect size (ES, in SD units) required for estimating our required sample size as follows:

(1) We used treatment ESs from the CAMS efficacy trial, which compared combined medication+CBT to monotherapies (medication alone, CBT alone) and placebo. CAMS reported quantitative anxiety outcomes using the Pediatric Anxiety Rating (PARS) scale. Outcomes did not differ significantly in CBT alone vs medication alone (though group mean differences on the PARS slightly favored medication over CBT). However, CAMS did find large ESs for combined medication+CBT compared to monotherapy, with a somewhat larger difference compared to CBT alone than medication alone.

(2) Using augmented CBT in CBT non-responders as the base, relative ESs reported at 24 weeks in CAMS were used as ES estimates for CBT + medication (i.e., medication added to CBT), medication alone, and medication+CBT (i.e., CBT added to medication). For Stage 1 remitters, we used an ES of 0.2 above their non-remitter counterpart.

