### Mediation analyses

We will perform mediation analyses on the Stage 1 main intervention effects and will follow the literature for development of statistical approaches for mediation analysis of SMART design adaptive interventions. We will test whether the common and specific factors in our causal pathway model significantly mediate the associations of treatment with patient outcomes. Let X be the assigned treatment, Y be 24-week outcomes, and M be the proposed mediator **(**Fig. 6**)**. We will assess mediation using 3 regression equations: 1) *Y* = *c*_1_*X* + *e*_1_, assessing the association of treatment with 24-week outcomes; 2) *M* = *aX* + *e*_2_, assessing the association of treatment with the putative mediator; and 3) *Y* = *c*_2_*X* + *bM* + *e*_3_, associating the association of treatment with 24-week outcome when adjusting for the mediator (termed the “direct effect” of X with Y). Age and sex will be included as covariates in all three equations. We will test whether the estimator of the indirect effect (*a x b*) differs significantly from zero using bias-corrected bootstrapped confidence intervals on the estimator. A significant mediating effect suggests that the association of treatment effects (X) with trial outcomes (Y) in regression (1) is in part explained by treatment effects on mediating outcomes (M) in regression (3).

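### The a × b mediation test on the CBT-versus-fluoxetine contrast does not test whether common factors relate to outcome within both treatments

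*Protocol article*

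**What the plan says.** The section on hypothesized causal pathways names four elements thought to drive improvement. Two of them, alliance-building and reward, are said to belong at least implicitly to medication treatment as well as to CBT. The section then commits: "Therefore, we will measure these elements over time in this SMART study and assess their influence on patient outcomes".

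The section Factors specific to Coping Cat CBT states two different expectations. The first is an association within each treatment, CBT and fluoxetine alike: "We expect that measures of each of the common factors will independently and positively associate with outcomes in our study for both". The second is that alliance will be greater with CBT and will partly mediate the outcome difference between the two modalities.

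Mediation analyses sets the test. Its scope is: "We will perform mediation analyses on the Stage 1 main intervention effects". It covers both kinds of factor: "We will test whether the common and specific factors in our causal pathway model significantly mediate the associations of treatment with patient outcomes". The second of its three equations gives path a, "assessing the association of treatment with the putative mediator". The criterion is whether a × b "differs significantly from zero using bias-corrected bootstrapped confidence intervals on the estimator". On adjustment it says: "Age and sex will be included as covariates in all three equations".

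**The concern.** The Stage 1 contrast sets one active treatment against another. Path a is therefore the difference in the factor between CBT-first and fluoxetine-first. It does not measure how much of the factor either treatment generates. The a × b test asks whether a factor accounts for the difference between arms, which matches the second expectation. It does not address the first, that the factor goes with better outcome in both arms.

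The mismatch is greatest where the causal model is most confident. The more nearly equal a factor is across the two treatments, the smaller a becomes, and the less a × b can show however strongly the factor drives improvement. As written, the first expectation has a hypothesis but no test, and a reader of the results would have only a × b to judge it by.

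**Working it through.** **Inputs from the protocol.** 404 randomized 1:1; 20% dropout; 324 completers (Sample size and power), so 162 per Stage 1 arm; two-sided 5% level; the three equations and the bootstrap criterion (Mediation analyses). The protocol gives no values for a or b. Those below are assumptions, in SD units.

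**The plan's own figures.** 404 × 0.80 = 323.2, stated as 324. Detectable Main Effect 1: (1.960 + 0.842) × √(2/162) = 2.802 × 0.1111 = 0.311, stated as 0.31. Both reproduce. No figure is stated for the mediation test.

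**Algebra.** With M = aX + e₂ and X the two Stage 1 arms, a is the between-arm difference in mean M. If a = 0, then a × b = 0 for every b.

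**Hand approximation.** With M standardized, SE(a) = √(2/162) = 0.111. When b is well estimated, a × b is significant about as often as a is:

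- a = 0.1: 0.1/0.111 = 0.90; P(Z > 1.06) = 14%
- a = 0.2: 1.80; P(Z > 0.16) = 44%
- a = 0.3: 2.70; P(Z > −0.74) = 77%
- a = 0.4: 3.60; P(Z > −1.64) = 95%

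**Simulation at n = 324.** M = aX + e, and Y depends on M with slope of size b and residual variance 1 − b². There is no direct effect, and age and sex are left out. Two interval methods were used: a distribution-of-product interval (2,000 data sets per cell) and the planned bias-corrected bootstrap (600 data sets per cell, 1,000 draws each).

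| Assumed a (SD) | Product interval, b = 0.2–0.4 | Bias-corrected bootstrap, b = 0.3–0.9 | By hand |
|---|---|---|---|
| 0 | 4–5% | 5–8% | 5% |
| 0.1 | 14–16% | 16–19% | 14% |
| 0.2 | 40–41% | 45–49% | 44% |
| 0.3 | not run | 74–81% | 77% |
| 0.4 | not run | 94–97% | 95% |

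At a = 0, raising b to 0.9 does not lift rejection (5.3%). In the same data sets the test of b adjusted for arm rejects in 95% at b = 0.2 and in about 100% at b = 0.3 or more. By hand at b = 0.2: SE(b) ≈ √(0.96/324) = 0.0544; 0.2/0.0544 = 3.67; P(Z > −1.71) = 96%.

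**Does anything else in the protocol test the first expectation?**

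- Equation 3 contains b adjusted for arm, but the text uses that equation for the direct effect and for the product. No test of b is stated.
- CBT fidelity measurement plans association analyses for Coping Cat adherence, dose and exposure, not for common factors.
- Process evaluation plans to measure acquisition of each core function, alliance and reward included, but states no test against outcome.
- The treatment-as-usual group is not randomized, and its reduced measure set omits the Outcome and Session Rating Scales. It cannot supply a contrast on alliance.

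**The case against.** The strongest reply is that a × b is a legitimate test of the question it is attached to, whether factors mediate the treatment–outcome association. Its 5% rejection at a = 0 is then correct type I error. That stands: a × b is right for the between-arm question and should be kept.

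The reply also corrects several stronger readings that a reader might infer:

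- **That the test can never detect a shared factor.** This holds only for equal sharing. The protocol says such elements are present to varying degrees and expects more alliance with CBT. At an assumed difference of 0.3–0.4 SD the test has about 74–97% power.
- **That a null will be reported as showing a factor is off the causal pathway.** No section says so. Mediation analyses interprets only a significant result.
- **That there is nothing to mediate.** Of the earlier multimodal trial the protocol says "Outcomes did not differ significantly in CBT alone vs medication alone". That concerns outcome, not the mediators. An indirect effect can exist without a total effect when direct and indirect effects oppose, and the protocol plans to classify such suppressive mediation.
- **That b is never estimated.** It is, in equation 3.

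A last reply is that model detail for a process analysis belongs in the analysis plan. That would excuse silence. Here the article itself fixes the equations, the covariates and the criterion, and these do not fit one of its two stated expectations.

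**Conclusion.** The concern holds in limited form. The written-out criterion for common factors answers whether they explain a difference between arms. It does not test the expectation that they associate with outcome in both therapies. For a factor delivered equally it rejects at about its nominal level (5–8% with the planned bootstrap). For a 0.2 SD difference it has about 40–49% power. These figures rest on assumed a and b, 162 completers per arm, standardized variables and no direct effect.

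The b already in equation 3 does not close the gap as specified. It carries no stated test, and baseline SCARED is not among its covariates. The timing of the mediator relative to the 24-week outcome is also not fixed. The protocol itself notes that better outcomes can precede and predict better alliance, so timing matters. Even a well-specified b is observational, because the factor is not randomized.

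This concerns a process analysis that is not among the numbered aims. The primary analysis and the sample size are untouched.

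**What to change.** In Mediation analyses, separate the two questions.

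1. Keep a × b on the Stage 1 contrast for explaining a between-arm difference. State that a null result is not evidence against a factor present in both arms.
2. For the expectation of association in both therapies, name the arm-adjusted path b as the test. Include baseline SCARED as a covariate, and the baseline value of the factor where it is measured. Report estimates within each Stage 1 arm and a treatment-by-factor term.
3. Fix the timing so that the factor precedes the outcome. For alliance and relatedness, use the monthly Outcome and Session Rating Scales. Table 2 schedules the reward measures (life satisfaction, well-being, social and school functioning) at baseline, week 12 and week 24 of the trial, not monthly. For these, use week 12 values to predict the week 24 outcome.
4. Label path b as observational.

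The cost is a few sentences of plan text and a small amount of extra regression on data already scheduled, with no added visits or participants.
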